## Abstract

**Background:** Studies within trials (SWATs) present an opportunity to examine design factors that may impact on the successful delivery of trials. One area in need of research is trial recruitment. Recruiting patients to trials is a major challenge facing trialists. Failure to meet recruitment targets can result in delays and underpowered studies. This SWAT evaluates the effectiveness of hand-held digital multimedia presentation of trial information and standard written patient information to potential participants on recruitment and retention to a host trial.

**Methods**: This is the protocol for SWAT 15, a two-group, embedded parallel randomised controlled trial (RCT) (ISRCTN12838042) designed within a host trial - the SATIN trial (ISRCTN88111427), a RCT designed for implementation in the Irish primary care setting. The SWAT eligibility criteria was determined by the host trial. General practices who agree to participate in the host trial will provide women (participants) who are willing to consider participating in the host trial with either a multimedia digital information resource facilitated through a handheld tablet device, plus a written participant information leaflet (Intervention) or a written participant information leaflet (comparator). Outcomes are recruitment and retention to the host SATIN trial and participant’s quality of decision-making.

**Discussion**: Although designed to be implemented in a host trial, the host trial, was suspended and therefore this SWAT was not implemented. The protocol and the lessons learnt whilst developing it offer guidance to researchers who wish to answer similar research questions in the future in a similar context or setting.

**Trial registration**: ISRCTN Registry
ISRCTN12838042 (11/10/2017)

## Background

Rigorous research is essential to delivering and improving the quality of health care. Randomised controlled trials (RCT) provide reliable evidence on the benefits and harms of healthcare interventions
^1^. Although RCTs are accepted as the most appropriate method to evaluate the effects of health care interventions, there is strong evidence that recruiting clinicians and patient participants to trials presents a significant challenge
^2^. Across trials, it is estimated that less than 50% meet their recruitment target or do so only with an extension to the original trial duration
^3,
4^. For example, of 114 trials funded by the UK Medical Research Council (MRC) and the Health Technology Assessment (HTA) Programme that recruited participants between 1994 and 2002, only 31% met their recruitment targets and over half (53%) were given an extension
^5^. More recently, Sully and colleagues investigated the recruitment success of 73 trials funded by the same bodies between 2002 and 2008 and observed similar results. Only 55% of trials recruited to their pre-specified target sample size and nearly half (45%) received an extension
^6^. Similar issues have also been recognised in the United States. A study investigating the prevalence and associated economic impact of low-enrolling clinical studies at a single academic medical centre found that of the 837 clinical studies terminated during the study period, nearly a third (31.1%) were low-enrolling. Furthermore, primary care trials often fail to achieve adequate sample size as demonstrated in a recent study of primary care trials in which only 23% recruited successfully compared to 62% of mental health trials
^6^. These failures in meeting recruitment targets mean that overall trial findings are likely to be underpowered; with the studies delayed and falling short of answering their objectives
^3,
6^.

Understanding how to maximise the recruitment process will help to overcome these challenges in the future and would benefit trialists during the design and implementation phases of trials
^4^. Developing and evaluating interventions aimed at improving recruitment to trials may be a good investment, where even a small return could translate into avoidance of substantial additional costs whilst reducing the time to potential knowledge impact. However, there is, as identified in a recent Cochrane systematic review, limited high quality evidence evaluating the effectiveness of interventions to improve trial recruitment
^7^. Furthermore, over 35% (24/68) of trials included in this review evaluated the effectiveness of recruitment strategies to hypothetical trials meaning that the effectiveness of the strategies evaluated in real-life settings is further limited.

Methodological innovation is necessary to improve the science of recruitment and should be a focus when seeking to improve trial recruitment. The importance of establishing new methods of effective engagement among patients, practitioners, and the primary care research community is paramount; as there is a propensity among researchers to overestimate the degree to which research is viewed positively by practitioners and patients
^8^. It is acknowledged that one barrier to patient recruitment is inadequacy of trial information to meet the needs of potential participants as well as the ineffective mode of dissemination of this information. A failure to adequately explain what the trial is about, what participation involves, and the value of participation to potential participants has a direct impact on the informed consent process
^9^.

Studies Within A Trial (SWATs) have been developed as one method of gathering information on different design factors potentially impacting on the outcome of trials
^10–
12^. SWATs seek to
*“aid the development of such research by increasing awareness of, and stimulating interest in the need for this research and providing a framework and resource to inspire and generate ideas, and to store, disseminate and modify such research”*
^13^. Researchers interested in conducting a SWAT are encouraged to register their SWAT in the
SWAT repository.

This SWAT was registered as
SWAT-15 in the SWAT repository. The host trial, SATIN (ISRCTN88111427); however, was stopped prior to recruitment of the first participant due to the emergence of new evidence on the treatment of urinary tract infections (UTI) and therefore this SWAT although designed was never implemented. The protocol and the lessons learnt whilst developing it could guide trialists who wish to answer similar research questions in the future. This protocol for SWAT-15, will be of use to researchers considering evaluating different ways to present information to potential trial participants and to those interested in SWATs in general.

## Aim

To evaluate the effectiveness of presenting potential trial participants with trial information using hand-held digital multimedia and written information leaflet or a standard written information leaflet, alone, on recruitment and retention to a host trial.

## Objectives

a) To establish if (a) the proportion of patients willing to consider participating and (b) the proportion of participants recruited to the host trial (in case this differs from the number of participants willing to participate, due to e.g. exclusion criterion) is improved using a hand-held multimedia presentation of trial information plus a standard written participant information leaflet compared to a standard written participant information leaflet, alone;b) To explore whether a hand-held multimedia presentation of trial information plus a standard written participant information leaflet improves retention of patient participants to the end of the host trial;c) To establish if the quality of decision-making as measured through a decisional scale, adapted from one used within the REFORM trial
^14^ and drawing conceptually on the SURE
^15^ and DelibeRATE scales
^16,
17^ is affected by the presentation mode (multimedia and written -v- written only) of participant information to patients.

## Methods

### Study design

A two-group, parallel embedded RCT using the SATIN trial as an example of how SWAT-15 could be implemented.

### Study population

The study population will be individuals who will be screened for and/or who are eligible to take part in the host SATIN trial.

***Inclusion criteria***

To participate in SWAT-15 individuals must, as determined by the host SATIN trial:

Be attending a general practice that is taking part in the trial;Have a GP-diagnosed UTI, and at least one of the symptoms of dysuria, urinary frequency, or urgency with/without low abdominal pain;Be a woman (non-pregnant) aged 18 years or above;Be able and willing to give written informed consent;Own a smartphone.

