### Assignment of interventions

Allocation will be performed at the individual patient level with half of the participants receiving:

a) Multimedia digital information resource facilitated through a handheld tablet device, plus a written participant information leaflet, within the general practice (n=230) (Intervention) (see extended data
^18^)ORb) Written participant information leaflet (n=230) (Comparator) (see extended data
^19^)

A cluster design could also be utilised but the resultant impact on study power would need to be considered. During the study period, potentially eligible participants (n=460) will be identified by the GP during their routine consultations based on the inclusion and exclusion criteria outlined above. Patients who are deemed eligible and willing to consider participating in the host study will be seen by a practice nurse or General Practitioner (GP). The practice nurse or GP will give consecutive eligible patients the next sequentially ordered, participant information leaflet, which will be taken from the top of the bundle of trial information pack. Attached to the participation information leaflet will be a sequentially numbered, sealed, opaque envelope with an ‘envelope ID’ number on it and a card inside with details of the woman’s group allocation. Group allocation will be determined by computer generation of a random allocation sequence with a 1:1 ratio and block sizes of 4, 8 and 8 (at random). As per allocation, the practice nurse or GP will give the potential participant either the patient information leaflet with a handheld tablet device and headphones to access the multimedia information (intervention) or no additional information i.e. the potential participant is given an information leaflet only (comparator). The practice nurse or GP will subsequently record the envelope ID number on the SATINs screening and enrolment log. The GP and/ or practice nurse will have been trained in the requirements of the host trial, and this SWAT, including in the use of the digital resource.

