### Informed consent

Informed consent will be sought for all women who decide to participate in the host trial, which was granted ethical approval from the Irish College of General Practitioners Ethics Committee (1
^st^ December 2016). Formal consent to participate in the SWAT, at the individual, patient-participant level will not be sought as this embedded study is not withholding information; instead the focus is on how it is presented. All potential participants will receive the host trial participant information leaflet approved by the Research Ethics Committee. Further, by telling participants that they are being randomised to different recruitment strategies would not only contaminate the results and undermine the intervention being tested, as it would unduly draw potential trial participant’s attention to the recruitment process, it would introduce complexity and likely confusion for participants due to the double consent present. There is precedence for this, as a similar approach has been used previously within the MRC START programme of research on the basis that the embedded study is not withholding information – just changing the way it is presented (while also presenting in traditional information leaflet format) (NRES Committee Yorkshire and the Humber – South Yorkshire (REC Reference 11/YH/0271)). Permission to proceed with the current study, without obtaining formal consent, was approved by the ICGP Ethics Committee (1st December, 2016).

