### Outcomes

***Primary outcome***

The primary outcome will be proportion of potentially eligible participants willing to participate in the host trial.

The number of eligible participants willing to consider participation (numerator) will be calculated as the number of participants who sign the host trial informed consent form (including those that are subsequently found not to fulfil the eligibility criteria). The denominator will be the number of potential participants who are randomised to receive either the intervention or comparator.

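### A host-trial criterion copied into SWAT-15 entry makes willingness to consent, which is the SWAT's primary outcome, a condition of being randomised

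*Protocol article*

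**What the plan says.** All references are to the protocol article.

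- **Inclusion criteria.** The list opens "To participate in SWAT-15 individuals must, as determined by the host SATIN trial" and includes "Be able and willing to give written informed consent".
- **Informed consent.** "Formal consent to participate in the SWAT, at the individual, patient-participant level will not be sought". The only consent in play is therefore consent to the host trial.
- **Assignment of interventions.** The GP identifies potentially eligible women by the listed inclusion and exclusion criteria. Then: "Patients who are deemed eligible and willing to consider participating in the host study will be seen by a practice nurse or General Practitioner (GP"). Leaflet and allocation envelope are handed over after that step.
- **Primary outcome.** "The primary outcome will be proportion of potentially eligible participants willing to participate in the host trial". The operational definition follows: "The number of eligible participants willing to consider participation (numerator) will be calculated as the number of participants who sign the host trial informed consent". Its denominator is every woman randomised in the SWAT. The Statistical analysis plan section repeats this definition.
- **Objectives.** The first part of objective (a) concerns "the proportion of patients willing to consider participating".
- **Sample size, estimated effect size and power.** With 64% of eligible women agreeing on written information alone, 460 women and α = 5%, the SWAT is said to have 80% power to detect 64% v 76%.

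**The concern.** A study of whether better information persuades more women to consent has to randomise women who might refuse. The inclusion list, read as it stands, requires them to be willing to consent first. A GP who follows the Inclusion criteria and Assignment of interventions sections faithfully could exclude reluctant women before any envelope is opened. Those are the women in whom the multimedia resource could make a difference. Both arms would then drift towards complete consent and the contrast would shrink towards zero. Analysis cannot recover this, because the excluded women are never randomised.

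Two related wording problems make it worse. The phrase about being willing to consider the trial describes both a step passed before randomisation (Assignment of interventions) and the outcome measured after it (Objectives, Primary outcome, Statistical analysis plan). And the 64% is attributed to eligible women, without saying whether they had already passed that step.

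The article is offered for reuse in other host trials, so an adopter would inherit the criterion.

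**Working it through.** **1. The entry rule against the outcome.** The inclusion list requires willingness to give written consent. The Informed consent section rules out SWAT consent, so host consent is meant. The primary numerator is the number who sign the host consent form, over all randomised. Entry rule and numerator therefore concern the same act. The sample size section expects 100% − 64% = 36% of control women not to agree. A population selected for willingness to consent cannot also contain 36% who decline.

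**2. The stated power.** Inputs: 230 per arm (Assignment of interventions), 64% v 76%, α = 5% (sample size section). Sidedness is not stated; two-sided is assumed. With pooled variance under the null and no continuity correction:

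- pooled proportion = (0.64 + 0.76)/2 = 0.70
- null standard error = √(2 × 0.70 × 0.30/230) = 0.0427
- alternative standard error = √((0.64 × 0.36 + 0.76 × 0.24)/230) = 0.0424
- z = (0.12 − 1.96 × 0.0427)/0.0424 ≈ 0.856, so power = 80.4%

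The required size is 228 per arm against 230 planned. The arithmetic is sound; the question is which women it describes.

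**3. The consent criterion applied before the envelope.** Suppose a fraction f of the 36% who would decline on the leaflet alone is screened out. Assume this removes persuadable women (12 points) and never-consenting women (24 points) in equal proportion. Then control = 0.64/(1 − 0.36f) and intervention = (0.64 + 0.12(1 − f))/(1 − 0.36f). At 230 per arm:

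| f (assumed) | Control | Intervention | Power |
|---|---|---|---|
| 0 | 64.0% | 76.0% | 80.4% |
| 0.25 | 70.3% | 80.2% | 69% |
| 0.50 | 78.0% | 85.4% | 53% |
| 0.75 | 87.7% | 91.8% | 31% |
| 0.90 | 94.7% | 96.4% | 15% |
| 1 (literal) | 100% | 100% | no contrast to test |

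**4. The planned relative gain has a ceiling.** The planned gain is 0.76/0.64 − 1 = 18.75%, printed as 18%. It is impossible once the control rate exceeds 1/1.1875 = 84.2% (or 1/1.18 = 84.7%).

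**5. The willing-to-consider step on its own.** If the 64% describes women before this step, the control rate among those randomised would be higher. Holding the planned odds ratio, (0.76/0.24)/(0.64/0.36) = 1.78, power at 230 per arm is 75% at a 70% control rate, 61% at 80%, 51% at 85% and 37% at 90%. An 80% control rate would need 20% of eligible women to drop out at that step (0.64/0.80 = 0.80). The article gives no such figure. If the 64% already describes women past the step, there is no loss.

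Steps 3 and 5 use different effect models and are not interchangeable. Both only illustrate what could happen.

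**The case against.** The strongest reply is that the literal reading conflicts with the rest of the article. The inclusion list is said to be determined by the host trial, and the consent line is ordinary host-entry wording. Willingness to give informed consent can hardly be settled before the information is given. Under Secondary outcomes, the patient ID is generated only after consent and is separate from the envelope ID. The denominator is all randomised, the numerator only those who sign, and the sample size section allows for 36% declining. This stands as evidence of intent. It does not remove the fault, because no sentence limits the criterion to host entry, and the Assignment of interventions section sends the GP to that same list.

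A reader might also infer three stronger things that the document does not support.

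- *That the first part of objective (a) cannot be affected by the intervention.* The Primary outcome and Statistical analysis plan sections define willingness to consider participation as signing the host consent form, which happens after randomisation. The intervention can affect it. What remains is one phrase with two meanings.
- *That the willing-to-consider step pushes the control rate above 64%.* The 64% is tied to women given written information only. They may already be the women who passed that step. The cited source is not at hand, so this cannot be settled either way.
- *That all GP-eligible women should be randomised.* Restricting to women open to the trial is a legitimate choice for a resource viewed in the practice over perhaps 15–20 minutes. Randomising women who decline at once would dilute the effect and require wider logging than the article plans.

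**Conclusion.** The concern holds for the inclusion criterion. As written, SWAT entry selects on the SWAT's own primary outcome and contradicts the 64% control assumption, and the bias is towards no difference. It must be corrected, but it is a copied host criterion, not proof that the trial would have failed; the harm depends on whether staff apply it before the envelope is opened.

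Applied literally, it leaves no contrast to test. Applied in part, it would give power of about 69% to 15% as the assumed screened-out fraction runs from 0.25 to 0.90, provided persuadable and never-consenting women are removed equally. The stated 80% power is correct for the population it assumes. Any loss from the willing-to-consider step (for example to about 61% at an 80% control rate with the odds ratio held) is conditional on assumed drop-out and is not shown by the document.

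**What to change.** 1. **Inclusion criteria.** For SWAT entry, require only that the woman is able to consent. State that willingness to consent applies to host-trial entry alone and is the SWAT's outcome.
2. **Objectives, Primary outcome, Statistical analysis plan.** Name the outcome throughout as signing the host consent form among women randomised in the SWAT. Keep the willing-to-consider phrase for the step before randomisation.
3. **Sample size, estimated effect size and power.** State that the 64% refers to women who have passed the willing-to-consider step. If it does not, restate the base rate and power for that group.

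The willing-to-consider step may stay. The first two changes cost only wording; the third needs a check of the source of the 64% and, if the denominators differ, a short recalculation. No change to the randomisation procedure or data collection is needed.

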***Exclusion criteria***

Exclusion criteria are as per the SATIN trial i.e., any signs of complicated infection or any condition that may lead to complications, current or recent antibiotic use, recent UTI, current intake of NSAIDs, pregnancy or breastfeeding, non-use of highly effective contraception, previous adverse reaction to any of the study drugs, current intake of drugs potentially interacting with the trial drugs, diabetes mellitus, chronic kidney disease or any other previous illness related to kidney or urinary tract, history of gastro-intestinal ulcers, Glucose 6 phosphate Dehydrogenase deficiency or any other medical condition that may put the participant at risk or influence the study results in the investigators’ opinion.

### Study setting

The SWAT will be carried out in general practices.

### Assignment of interventions

Allocation will be performed at the individual patient level with half of the participants receiving:

a) Multimedia digital information resource facilitated through a handheld tablet device, plus a written participant information leaflet, within the general practice (n=230) (Intervention) (see extended data
^18^)ORb) Written participant information leaflet (n=230) (Comparator) (see extended data
^19^)

A cluster design could also be utilised but the resultant impact on study power would need to be considered. During the study period, potentially eligible participants (n=460) will be identified by the GP during their routine consultations based on the inclusion and exclusion criteria outlined above. Patients who are deemed eligible and willing to consider participating in the host study will be seen by a practice nurse or General Practitioner (GP). The practice nurse or GP will give consecutive eligible patients the next sequentially ordered, participant information leaflet, which will be taken from the top of the bundle of trial information pack. Attached to the participation information leaflet will be a sequentially numbered, sealed, opaque envelope with an ‘envelope ID’ number on it and a card inside with details of the woman’s group allocation. Group allocation will be determined by computer generation of a random allocation sequence with a 1:1 ratio and block sizes of 4, 8 and 8 (at random). As per allocation, the practice nurse or GP will give the potential participant either the patient information leaflet with a handheld tablet device and headphones to access the multimedia information (intervention) or no additional information i.e. the potential participant is given an information leaflet only (comparator). The practice nurse or GP will subsequently record the envelope ID number on the SATINs screening and enrolment log. The GP and/ or practice nurse will have been trained in the requirements of the host trial, and this SWAT, including in the use of the digital resource.

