***Secondary outcomes***

a) The proportion of participants recruited to the host trial (in case this differs from the number of participants willing to participate, due to, for example, an exclusion criterion).

This will be recorded in the host trial electronic case report form (eCRF) (or equivalent). The host trial research team will share the number of recruited participants to their study (i.e., the number of participants who sign a consent form and complete screening through the eCRF) with the SWAT research team. Demographic information (i.e., age, education, number of children, health insurance status) will be collected as part of the host study from participants who give informed consent and shared with the SWAT team. All data will be aggregated and anonymous and it will not be possible for the SWAT research team to identify individual participants.

The nurse/ GP will complete a screening and enrollment log for all patients who are willing to consider participating in the study. Any patient who receives the study intervention or comparator will be allocated an envelope ID number and this will be recorded on the screening and enrollment log. The envelope ID number is the key to identifying the intervention to which participants were randomised.

The practice nurse will also record the patient ID number on the screening and enrollment log form. A patient ID is generated within the eCRF when it is opened and the patient has given informed consent to participate. The patient ID will allow the SWAT team to identify if the demographic characteristics differ between consenting patients in the intervention and comparator groups.

b) The proportion of recruited participants who are retained to the end of the host trial;

Retention will be measured as the number of participants who complete outcome measures in the host trial.

c) The quality of decision-making

Quality of decision-making will measure the women’s understanding of participating in the host trial. The quality of decision-making by potential host trial participants will be measured through the completion of a decisional scale, adapted from one used within the REFORM trial
^14^ and drawing conceptually on the SURE
^15^ and DelibeRATE scales
^16,
17^. The SWAT research team will analyse these data after the host study has finished recruiting and the last patient has completed the study.

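### Envelope IDs are logged only after delivery, and the allocation card travels with the leaflet: refusals could go uncounted and the SWAT randomisation could be disclosed

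*Protocol article*

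**What the plan says.** The protocol article sets out the steps under Assignment of interventions. The allocation device is described first: "Attached to the participation information leaflet will be a sequentially numbered, sealed, opaque envelope with an ‘envelope ID’ number on it", with "a card inside with details of the woman’s group allocation". Delivery follows: "As per allocation, the practice nurse or GP will give the potential participant either the patient information leaflet with a handheld tablet device and headphones", or the leaflet alone in the comparator arm. Logging comes last: "The practice nurse or GP will subsequently record the envelope ID number on the SATINs screening and enrolment log".

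Under Primary outcome, and again under Statistical analysis plan, the denominator is everyone allocated: "The denominator will be the number of potential participants who are randomised to receive either the intervention or comparator". The numerator is women who sign the host consent form.

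Under Secondary outcomes (a), the log is kept for every patient open to considering the study, and the rule for the ID reads: "Any patient who receives the study intervention or comparator will be allocated an envelope ID number", to be entered on the log. The same section makes the envelope ID the means of identifying a woman's arm. The patient ID is created in the eCRF only once consent has been given.

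Under Informed consent, one reason for not seeking SWAT consent is that "telling participants that they are being randomised to different recruitment strategies would not only contaminate the results".

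**The concern.** The primary outcome is signing against not signing, and the two groups leave different traces. A woman who signs has an eCRF record and a patient ID, so her missing envelope ID would be noticed. A woman who declines has only the log entry. Incomplete logging would therefore remove almost only non-events and push a proportion upwards.

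The person making the entry knows the arm, since nobody can deliver the allocated material without knowing it. The arms also differ in handling: a tablet, headphones and perhaps 15 to 20 minutes (Intervention design) against a leaflet. It is plausible that women who leave or turn the material down would be logged unequally. If that happened, the comparison of arms would be biased.

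The wording leaves a gap as well. The denominator is tied to randomisation, but the logging rule is tied to receipt. A woman whose envelope has been opened and who then declines the tablet belongs in the denominator, yet the rule does not clearly require her ID to be recorded.

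The second issue is disclosure. The card stating the allocation is attached to the document handed to the woman, and no step separates them. If she saw it, she would learn what the Informed consent section says would contaminate the results.

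**Working it through.** **The plan's own figure.** Inputs from Sample size, estimated effect size and power, and from Assignment of interventions: 64% against 76%, 230 per arm, α = 5%. Sidedness is not stated, so two-sided is taken.

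- Mean proportion = (0.64 + 0.76)/2 = 0.70.
- Standard error under no difference = √(2 × 0.70 × 0.30/230) = 0.0427.
- Standard error under the alternative = √((0.64 × 0.36 + 0.76 × 0.24)/230) = 0.0424.
- Power = Φ[(0.12 − 1.96 × 0.0427)/0.0424] = Φ(0.856) = 80.4%.

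The stated 80% is reproduced. It stands if every randomised woman is counted.

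**Illustration of incomplete logging.** The documents give no loss rate, so the fraction f below is an assumption. Let the true proportion signing be 64% in both arms. (The protocol gives 64% as a recruitment proportion; it is applied here to signing consent.) Expected refusals per arm are 230 × 0.36 = 82.8. If a fraction f of them goes unlogged in one arm only, that arm's apparent proportion is

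0.64/(1 − 0.36f).

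The type I error comes from 200,000 simulated trials. Signers are drawn as binomial(230, 0.64) in each arm, each refusal in one arm is kept with probability 1 − f, and a pooled two-sided z test is applied.

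| f (assumed, one arm only) | Refusals lost | Apparent proportion | Spurious difference | Type I error |
|---|---|---|---|---|
| 0 | 0 | 64.0% | 0 | 4.9% |
| 5% | 4.1 | 0.64/0.982 = 65.2% | 1.2 points | 5.8% |
| 10% | 8.3 | 0.64/0.964 = 66.4% | 2.4 points | 8.3% |
| 20% | 16.6 | 0.64/0.928 = 69.0% | 5.0 points | 19.8% |

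**Equal loss in both arms.** With no true effect, both proportions rise by the same amount and no spurious difference appears. With 64% against 76%, the 12-point difference shrinks to 11.5 points at f = 10% (77.9% − 66.4%) and to 10.9 points at f = 20% (79.8% − 69.0%, from unrounded values).

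**Disclosure.** No arithmetic applies. Assignment of interventions attaches the envelope to the leaflet and gives the leaflet to the woman. Informed consent relies on her not being told of the randomisation. The article does not say who opens the envelope or where the card goes afterwards.

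**The case against.** The strongest reply is that the protocol already requires the entry. The log covers every patient open to considering the study, a step that comes before the envelope, and the ID rule does not depend on consent. Losing refusals would be non-compliance. That stands, and it rules out reading the plan as one that drops refusals by design. It does not remove the mismatch between randomised and receives.

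A reader might infer that the ID is logged only once the woman has decided. The text does not say so: it places logging after delivery, and with 15 to 20 minutes of material an entry at hand-over could precede her decision. That staff open the envelope is likewise an inference from their having to deliver as allocated.

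A reader might also infer that lost refusals could never be found. That is too strong. Envelopes are sequentially numbered and taken in order, so a missing number would usually show as a gap, and the allocation sequence would identify its arm. What remains is that no such check is described. Site procedures of that kind may sit in a fuller document, so the absence alone is not an error. The order of steps, however, is fixed by the article itself.

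On disclosure, the waiver does not say that the allocation must stay hidden. It objects to telling women that they are being randomised to recruitment strategies, and nothing says that a woman reads the card. This is a risk left open by the stated handling, not a contradiction.

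Finally, nothing in the documents supports any particular loss rate, its confinement to one arm, or its direction. That is correct, and it limits the table to illustration.

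**Conclusion.** The point holds as a cheap improvement to a stated sequence that is weaker than it needs to be. Staff who know the arm make the only record of a refusal after delivering the material, and the logging rule is worded on receipt while the denominator is worded on randomisation. No error in the stated power follows.

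The size of any bias cannot be derived from the documents. Under the assumed one-arm losses it ranges from slight (about 4 women, type I error 5.8%) to serious (about 17 women, about 20%). It requires unequal loss, and its direction depends on which arm is affected.

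The disclosure risk is separate and rests on the absence of a step to detach the envelope. Both matter although the SWAT never ran, because the article offers the protocol for use elsewhere and anticipates pooling of results.

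**What to change.** - **Assignment of interventions:** have staff detach the envelope from the leaflet, write its ID on the log before opening it, keep the card, and only then hand over the leaflet, with the tablet where allocated.
- **Secondary outcomes (a):** align the logging rule with the Primary outcome section, so that every opened envelope counts in the denominator whether or not the woman goes on to take or view the material.
- **Reconciliation:** at each practice, check used envelope numbers against the log.

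The cost is one log column, a line in staff training and an envelope count per practice. The sample size and randomisation scheme are unchanged.
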